## Abstract

**Background:**

The health care system in Thailand has struggled to cope with the COVID-19 pandemic, resulting in decreased administration of community-based directly observed therapy (DOT) for tuberculosis (TB). As an alternative to failed DOT, video-observed therapy (VOT) or the Thai asynchronous VOT system, “TH VOT,” was devised. We developed a protocol for a study to test the superiority of VOT over DOT in ensuring treatment compliance.

**Objective:**

We aim to compare the mean cumulative compliance days of TB patients and their observers under the VOT program with that of individuals under the DOT program during the intensive phase of TB treatment.

**Methods:**

A cluster randomized controlled trial of pulmonary TB patients and their observers will be conducted over a 2-month period. This study will be conducted in the Hat Yai and Meuang Songkhla districts of Songkhla Province, Southern Thailand. A total of 38 observers working at 38 primary care units (PCUs) will be randomized equally into VOT and DOT groups. The TH VOT system will be implemented in 19 PCUs in the VOT group while the other 19 PCUs will continue with the traditional DOT program. Approximately 1-5 TB patients will be under observation, depending on the PCU jurisdiction in which the patients reside. The inclusion criteria for TB patients will be as follows: patients diagnosed with newly active pulmonary TB with a positive acid-fast bacilli sputum smear, aged >18 years, own a smartphone, and are able to use the LINE (Line Corporation) app. The exclusion criteria will be patients with a condition that requires the intervention of a specialist, rifampicin resistance according to a cartridge-based nucleic acid amplification test (GeneXpert MTB/RIF), unable to continue the treatment, and/or alcohol dependence. After the 2-month observation period, all sessions and follow-up clinical outcomes recorded will be retrieved. An intention-to-treat analysis will be performed to assess the compliance of both patients undergoing drug administration and their observers.

**Results:**

The Human Research Ethics Committee, Faculty of Medicine, Prince of Songkla University approved the trial on February 19, 2021 (approval number 64-03618-9). The trial was funded in May 2021. The recruitment period will be from January 2022 to July 2022. The observation is scheduled to end by September 2022.

**Conclusions:**

If the VOT shows superiority in observational compliance among patients and observers, the existing DOT policy will be replaced with VOT.

**Trial Registration:**

Thai Clinical Trials Registry TCTR20210624002; https://www.thaiclinicaltrials.org/show/TCTR20210624002

**International Registered Report Identifier (IRRID):**

DERR1-10.2196/38796

## Introduction

Thailand is one of the 30 countries worldwide with the greatest tuberculosis (TB) burden [1]. During the past 2 years, Thailand has also been heavily impacted by the COVID-19 pandemic [2-4]. The pandemic led to a reduced frequency of administration of the existing community-based directly observed therapy (DOT) for TB patients and irregularity in its implementation [5-7].

Recently, a new strategy called “video-observed therapy” (VOT) was developed, which enables the provision of remote observation for patients with TB in contrast to conventional DOT. There are two forms of VOT: synchronous VOT (S-VOT) and asynchronous VOT (A-VOT) [8]. With S-VOT, observers video call their patients for real-time observation of drug administration, whereas with A-VOT, observers can review the video sent by patients at any time. Globally, A-VOT is more commonly used than S-VOT because it allows patients to record drug-administration sessions at their convenience; moreover, the video can be watched multiple times [8]. Thus, Thailand uses an A-VOT system to collect video records that can be audited [9]. Instead of a home visit in a community, an observer can flexibly use the A-VOT system to lower their travel costs and risk of SARS-CoV-2 infection.

Previous studies reported that in western countries, A-VOT has better patient compliance, cost utility, and acceptability than DOT [10-13]. However, these studies assessed A-VOT according to the number of observations of clinic-based and comprehensive community-based DOT. The irregular community-based DOT in Thailand cannot be applied to these previous studies that were conducted at an individual patient level. Owing to irregularities of DOT compliance among observers in Thailand [5], it is important to consider observation of therapy at the observer level.

To ensure an unbiased comparison between VOT and DOT, a cluster randomized controlled trial will be conducted based on a series of 2-month observations among pulmonary TB patients and their observers. A cluster randomized controlled trial design is required because in the Thai health system, patients within the same jurisdiction are observed by the same observers working at the primary care unit (PCU) of the jurisdiction.

The primary objective of this trial is to compare the mean cumulative number of compliance days of TB patients and their observers under the A-VOT program with those under the traditional community DOT program. In each jurisdiction, patient compliance with self-reporting daily drug-administration sessions and the number of doses observed will be assessed at an individual level. Patients in the same jurisdiction will represent a cluster and will be observed by the same observer. After 60 days of the intensive phase of TB treatment, the mean cumulative number of the patients’ days with self-reporting and being observed in the VOT group and the DOT group will be compared at a cluster level. The secondary objectives include performing a descriptive review of the compliance activities and comparing the clinical outcomes between patients in the VOT and DOT groups. The clinical outcomes of sputum conversion and reporting of adverse events will also be ascertained, and statistically significant differences in the secondary outcomes between the VOT and DOT groups are not expected.

## Methods

### Study Setting

This study will be conducted in the Hat Yai and Meuang Songkhla districts of Songkhla Province, Southern Thailand, where a robust internet network is available. The study setting is based on 53 PCUs in the province, each including a TB staff member who worked as a DOT observer for at least 2 years. All people in the setting are regular smartphone users.

### Background of the Existing A-VOT in Thailand

An A-VOT in Thailand (ie, the “TH VOT” system) was developed to enable remote observation of administration of anti-TB drugs taken by patients with TB [7]. The TH VOT system is a secured web system that allows patients and their observers to make a daily appointment for an observation session [14]. The system is compatible with any mobile web browsers without the requirement for installation of an additional app. A TH VOT app is also available on the Google Play store as an alternative platform that uses the system [15]. The patients and observers can easily register and use this VOT system through user authentication of the LINE (Line Corporation) app, which is the most commonly used app in Thailand [16-18]. With daily autonotification, both patients and observers will be notified about their appointment. The patients record themselves while taking their medication and upload the video to the server. The server then notifies the observer to review the video. Data regarding patient and observer compliance will be assessed according to our previous study protocol [9]. The usability of the system was tested during November 2021. It was found to function well with no technical problems and was usable among both TB patients and observers [9].

### Study Design

We will perform a cluster randomized controlled trial. An observer will be assigned a cluster of patients with pulmonary TB that live in the same jurisdiction, either using DOT or VOT. We aim to observe each patient for 60 days during the intensive phase of their TB treatment. Daily compliance will be audited by one auditor who will supervise all observers in the study area according to a standard assessment protocol [9]. The study flow is summarized in Figure 1.

**Figure 1 figure1:**
[figure not shown]
Study flow. c: number of clusters; n: number of patients with tuberculosis; DOT: directly observed therapy; TH VOT: Thailand's asynchronous video-observed therapy system; VOT: video-observed therapy.

### Participants

#### Patients (Individual Level)

Patients will be considered eligible if they have newly active pulmonary TB diagnosed with a positive acid-fast bacilli (AFB) sputum smear, are aged>18 years, own a smartphone, and are able to use the LINE app. Participants are excluded if they have a condition that requires a specialist’s intervention, have rifampicin-resistant TB as tested by GeneXpert, unable or ineligible to continue the treatment for 60 days, or have alcohol dependence.

#### Observers (Cluster Level)

There are 53 PCUs in the study area. Based on a random list of the PCU numbers generated using R software (1-53), the observers in the PCUs numbered 1 to 38 will be randomly allocated to groups. If they refuse to undergo allocation, the observers in the PCUs numbered 39 to 53 will be subsequently invited until 38 observers have been allocated.

### Cointerventions

The following criteria will be applied to all patients and observers, regardless of their treatment group.

Patients with pulmonary TB will be diagnosed and treated by a general physician at Hat Yai Hospital or Songkhla Hospital. After diagnosis, the patients will be referred to the TB clinic. The patients will be provided zipped bags daily for 60 days, each with a daily dose of their isoniazid, rifampicin, pyrazinamide, and ethambutol (HRZE) drug regimen [7]. Patients who consent will be registered in the database by a TB nurse. The patients will be scheduled to take their medications (HRZE regimen) once a day. After each patient registration, the observer in the jurisdiction where the patient resides will be notified through autonotification on the official LINE app (either DOT or VOT).

For monetary compensation, the patients will receive 300 baht (US $8.68) immediately after registration to cover the cellular internet cost for the first month. Further compensation will be paid once the patients complete their 60-day intensive treatment without discontinuing the assigned intervention. They will receive 300 baht (US $8.68) to reimburse the cellular internet cost for the second month and 400 baht (US $11.57) for transportation of the sputum specimen for 3 consecutive days.

The observers will be compensated 600 baht (US $17.36) if they observe medication administration among patients for at least 15 out of 60 daily sessions. They will also be compensated for the cost of travel to visit their patients (4 baht or US $0.12 per kilometer).

Apart from the assigned intervention, the care of the patients at the TB clinic will remain the same as that during routine clinical practice. In the event of any suspected adverse events, the patients or their families will be able to phone the TB clinic for advice.

### Assigned Interventions

#### Individual Level

##### VOT for Patients

After registration, TB patients in the VOT jurisdiction will be trained by the TB nurse regarding how to log in to the TH VOT system through the official LINE app, and record and upload a drug-taking video session according to the standard operating procedure (SOP) [7]. Briefly, the patients must set their video frame for clear visibility of their face. All tablets and capsules should also be clearly visible. Patients should pick up the pills from the drug plane (see [7]) and put them on their tongue. Next, they should swallow the pills with clear water from a (clear) glass, raise their tongue to show the sublingual area, and stick out their tongue to show the palate area.

##### DOT for Patients

For patients in the DOT jurisdiction, the TB nurse will provide a booklet for recording daily drug intake and whether the intake is observed by the assigned observer. The TB nurse will request the patients to return the booklet and all zipped bags on the follow-up day to claim their compensation. Each weekend, the auditor will notify the patients to capture and send the most recent page of the booklet to the official LINE chat, to which the observers do not have access.

#### Cluster Level

##### VOT for Observers

To avoid a learning curve on the VOT side, the observers will be trained to demonstrate to the patient on how to correctly record and approve the recorded video according to the SOP [7]. They will be required to undergo real or simulated activities for 1 month before the trial [9].

After being notified about patient recruitment, the observers will visit patients at home on the first day. They will confirm whether the patient can record the video according to the SOP [7]. The observer and the patient will set an appointment time for medication administration. Next, the patient will keep a daily record of the drug-taking session, note any adverse events, and send the video to the observer through the TH VOT system. The observer will review the video, approve the session, and provide any necessary advice through the LINE chat box. The observer will follow up with a phone call if the patient fails to send the video within 30 minutes of the appointment.

##### DOT for Observers

Based on the guideline provided by the National Tuberculosis Information Program (NTIP) [19], which specifies that only the observer takes notes, we added an instruction regarding TB patients self-recording their daily drug-taking session.

After being notified by the automatic system, the observer will conduct home-visit DOT as routine treatment. To validate the observer’s recorded information, every weekend, the patient and the observer will be requested to take a photo of the most recent page of the booklet and send it to the auditor through the TH VOT official LINE system. The auditor will review these and record the number of daily compliant sessions in the database.

### Procedures for the Auditor to Review Each Video/Picture Session

#### Sessions in the VOT Group

“Day” will be used as the time unit for judging compliance, and local times (Greenwich Mean Time+7 hours) will be recorded. The morning will begin at 12 AM (midnight) and the evening will end at 11:59 PM. However, daily compliance will be judged as “achieved within the cut-off time” if the patients take their medication and submit their videos before 6 AM the following day. The auditor will assess daily video sessions for patients within 24 hours of the video upload. Assessment items include whether the VOT has been administered, if the patients followed the SOP, and whether they were observed as per the protocol or properly reminded by their observer. The auditor will interpret each session based on the SOP modified from the previous study [9].

The patient will be considered to have daily compliance if the video is sent within the stipulated time and if its quality meets the following criteria: (1) the patient’s face and the drug tablets/capsules are clearly visible in the video frame, (2) the pills are picked up from the drug plane and placed on the tongue, (3) the pills are swallowed with water from a (clear) glass, (4) the tongue is raised to show the sublingual area and stuck out to show the palate area, and (5) steps 2 to 4 are repeated until all pills are consumed.

The observers will be considered compliant if they adhere to the following quality standards: (1) correctly assess whether the patient performs the aforementioned steps, (2) note the number of pills consumed by the patient in the video correctly, and (3) follow up with patients via phone calls if they perform any procedure incorrectly. The TH VOT system can detect whether the observers have already made a phone call to their patients.

The daily session scored by the auditor will be recorded as 1 for daily compliance or 0 otherwise. The approval platform of the TH VOT system will automatically save all lists of the steps approved and the daily compliance score to the server database. If a patient does not record a video following the SOP, the auditor will make a phone call to remind the observer to correct the patient’s mistakes. If a patient does not send a video for 7 consecutive days, they will be considered to have discontinued the intervention.

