#### Sessions in the DOT Group

The auditor will score the daily compliance weekly based on the booklet photos sent by the TB patients and their observers. The patients will be considered to have daily compliance as reported (no audit). The auditor will make a phone call to the TB patients to confirm if they were observed as reported by their observer and to remind them to safely store the booklet and all zipped bags received from the TB clinic. If the patients report that they were not observed, the auditor will further investigate and record the observer’s actions such as making phone calls instead of in-person visits to check patients’ daily drug administration, missing patient appointments, or performing activities not included in the in-person DOT protocol.

A daily session reported by the observer will be scored as 1 for daily compliance as confirmed by the patients and 0 otherwise. If a patient misses a phone call twice or loses the booklet and/or the blank zipped bags, they will be discontinued from the intervention and their daily scores of the previous 7 days will be 0. All scored sessions will be recorded in the DOT record system of the server. The activities of observers not included in the in-person DOT will also be recorded.

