### Outcomes

#### Primary Outcomes

Data recorded by the auditor will be compiled to understand the compliance of patients and observers in each arm. For compliance of the individual TB patients, the daily compliance scores rated by the auditor will be summed and divided by 60 (for the 60 days of observation) to obtain the percentage of cumulative days with compliance. For the whole group of patients, the mean cumulative number of compliance days will be calculated, taking the clusters into account.

Similarly, for compliance of the individual observers, the daily compliance score rated by the auditor will be calculated. The individual compliance unit of an observer will be the number of days each patient is actually observed. A higher number of patient doses observed will increase the overall contribution of the observer to the mean cumulative number of compliance days for the whole group of observers (VOT or DOT).

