### Potential Strengths

This study will assess the compliance effect on both patients and their observers in a cluster, which is more practical than using an individual effect. Compliance of both patients and observers under community-based DOT, which has rarely been studied, will be assessed in this cluster randomized superiority trial. Although treatment group blinding is not possible [24], both groups will be under the same level of monitoring by the auditor. Thus, the Hawthorne effect will be balanced.

Previous VOT versus DOT comparative studies [10,11] have been based on an overall assessment, including ordinary percentage of compliance. Our mean cumulative function analysis will determine periods with weak compliance. This can be used to reinforce observation compliance in the future.

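### The observer primary outcome is scored on a different basis in each arm, so the article's claims of equal monitoring and of certain VOT superiority are unsupported

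*Protocol article*

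**What the plan says.** **VOT arm** (Sessions in the VOT Group; VOT for Observers).
- Timing: "The auditor will assess daily video sessions for patients within 24 hours of the video upload".
- Among the items assessed is "whether they were observed as per the protocol or properly reminded by their observer".
- An observer is compliant on meeting three standards: judging the patient's steps correctly, recording the pill count from the video correctly, and "follow up with patients via phone calls if they perform any procedure incorrectly".
- If no video arrives: "The observer will follow up with a phone call if the patient fails to send the video within 30 minutes of the appointment".
- If a video departs from the SOP, "the auditor will make a phone call to remind the observer to correct" the patient's mistakes.

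**DOT arm** (Sessions in the DOT Group). The auditor scores once a week from booklet photos. A session reported by the observer scores 1 if the patient confirms it and 0 otherwise. Where the patient says no observation took place, the auditor records what the observer did, and the examples given include "making phone calls instead of in-person visits".

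**Outcome definition** (Primary Outcomes). "The individual compliance unit of an observer will be the number of days each patient is actually observed". Reminders are not mentioned.

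**Discussion.** Potential Strengths states that "both groups will be under the same level of monitoring by the auditor" and concludes that the Hawthorne effect is balanced. Limitations says DOT compliance may be over-reported, and infers that if DOT still comes out lower, VOT's superiority is certain.

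**The concern.** Observer compliance is a primary outcome and the one named in Sample Size as the basis of the design. The Discussion summary presents it as the comparison the trial will settle, and the Conclusion ties replacement of DOT to it.

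Three features disturb that comparison:
1. A telephone contact can form part of compliant behaviour in VOT, while in DOT it is listed as an example of non-observation.
2. The outcome assessor intervenes with the person being scored, about the behaviour being scored, in one arm only. Nothing says the score is fixed before that intervention.
3. The article describes monitoring as equal and names one bias only, which runs against VOT. A reader would therefore treat any VOT advantage as conservative.

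If some VOT credit comes from reminders or prompted calls, part of an observed difference would reflect the scoring rules and not more doses being watched.

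**Working it through.** **Step 1. Score the same kind of day in each arm.**

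| Day | VOT observer | DOT observer |
|---|---|---|
| Dose session seen and done properly | 1 if judged and counted correctly | 1 if reported and the patient confirms |
| Session seen but done wrongly | 1 if judged and counted correctly and the patient is phoned; the patient scores 0 | No equivalent audit of technique |
| Session not seen, observer phones | Unsettled: the assessment item mentions reminding, but the first two standards need a video and Primary Outcomes needs observation | 0 by inference, since the call is recorded after the patient denies being observed |
| Session not seen, no contact | 0 | 0 |

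The third row is the gap. The second row is a difference of standard, but it need not conflict with Primary Outcomes, because the observer did watch the session.

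**Step 2. Compare monitoring.** VOT sessions are reviewed within 24 hours of upload, and SOP departures trigger an auditor call to the observer. The observer's own call to the patient is the third scored standard, so the prompt concerns a scored action. DOT observers are asked for a booklet photo every weekend, scoring is weekly, and the auditor's described calls go to patients. No auditor prompt to DOT observers about missed observation is described. These are not the same level of monitoring.

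**Step 3. Size of the phone-only component.** The plan's own contrast comes first: 65 − 100 × 1/60 = 63.3 points, which Sample Size gives as 64. The 65% is a patient figure from the earlier study, not an observer figure.

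No call frequency is given, so what follows is an illustration under assumptions. Suppose there is no true difference: both arms observe a share p of days, and observers in both arms phone on a share q of the remaining days. If those calls score 1 in VOT and 0 in DOT:

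Artificial difference = [p + (1 − p)q] − p = (1 − p)q

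| p | q = 0.10 | q = 0.25 | q = 0.50 |
|---|---|---|---|
| 1/60 | 9.8 points (5.9 days) | 24.6 points (14.8 days) | 49.2 points (29.5 days) |
| 0.65 | 3.5 points (2.1 days) | 8.8 points (5.2 days) | 17.5 points (10.5 days) |

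Days are points × 60/100. The two values of p are the plan's own DOT and VOT figures, used as bounds. If Primary Outcomes governs and reminders never count, every cell is 0.

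**Step 4. Test the inference in Limitations.** It is valid only if every bias runs against VOT. Possible reminder credit and auditor prompts run toward VOT. DOT over-reporting and the stricter audited standards for VOT observers run against it. With biases in both directions, a lower DOT result does not by itself establish superiority.

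**The case against.** The strongest reply is that reminder credit is a reading and not a rule. The phrase about reminding is an assessment item. The observer standards are three and joined by *and*, and the first two presuppose a video, so a call alone does not satisfy them. On a faulty-video day the VOT call supplements a session the observer watched, whereas the DOT call replaces a visit, so these are not the same behaviour scored in opposite ways. The auditor's prompt covers SOP-breaking videos and not every missed day, and whether a prompted call earns credit is not stated. Detailed scoring follows an SOP that is not shown.

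Most of this stands. It confines the scoring ambiguity to no-video days and to prompted calls. It does not reconcile the assessment item with Primary Outcomes, and it does not rescue the claim of equal monitoring.

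A reader might go further and infer that the contrast favours VOT by construction. The documents do not support that for the net result: VOT observers are audited on judgement and pill count, while DOT rests on reports that Limitations itself says may be overstated.

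A reader might also take 100 − 65 = 35 points (21 of 60 days) as the size of the artefact. That is only an upper bound. It uses a patient figure, pools faulty with absent videos, and needs a credited call on every remaining day.

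**Conclusion.** The point holds in limited form. The observer outcome rests on different scoring rules in the two arms, and the score for VOT days with a reminder but no video is not settled between Sessions in the VOT Group and Primary Outcomes. The statements of equal monitoring and a balanced Hawthorne effect are contradicted by the described procedures. The inference of certain superiority fails because it weighs only one of several biases.

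Neither the net direction nor the size can be derived. The phone-only component is 3.5 to 17.5 points for q from 0.10 to 0.50 at p = 0.65, larger at lower p, and zero if Primary Outcomes governs. This assumes equal true observation and equal calling in both arms, with credit in VOT only. It would also be too strong to say that no positive difference could reflect more observation. If something near the planned 65% against 1/60 were seen, with the 65% made up of reviewed videos, most of the gap would be real observation.

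**What to change.** 1. **One primary definition in both arms.** An observer-day scores 1 only if the observer saw that day's dose session: a video reviewed and correctly assessed, whether approved or rejected, or an in-person visit confirmed by the patient. Credit should not depend on approval, because that would penalise an observer who correctly rejects a faulty video and would merge observer with patient compliance.
2. **Phone-only days** score 0 in both arms and are reported descriptively by arm.
3. **Auditor prompts.** Base the VOT observer score on actions taken before any auditor prompt. If prompt times are not stored, flag prompted days and remove their credit in a sensitivity analysis.
4. **Discussion.** Replace the equal-monitoring and Hawthorne statements with the actual difference: VOT review within 24 hours with prompts to observers, against weekly DOT scoring with calls to patients. Replace the certain-superiority inference with an account of biases in both directions.

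**Cost.** Mainly wording and a database query. VOT approvals are already saved, the system detects observers' calls, and DOT activities outside in-person observation are already recorded. Auditor prompts must be logged, since the article does not say whether their times are kept. VOT observer compliance may come out somewhat lower.
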